#### Outcome measures

The primary outcome is a reduction in alcohol intake measured by the modified Alcohol Use Disorders Identification Test (AUDIT) [24]. As there is limited experience of suitable measures for interventions for substance misuse in this population, the percentage of days of abstinence (PDAS) and percentage of days of heavy drinking (PDHD) will also be calculated. Definition of heavy drinking will be informed by a literature review [26]. These additional indices have been included in order to estimate which outcome may perform most reliably for a sample calculation for a definitive trial.

Secondary outcomes will be willingness to change, health status, service use, health-related quality of life and mental status.

#### Instruments

Instruments used in the trial will include the following:AUDIT [24], which is a screening tool for identification of excessive drinking, an aid to brief interventions, and it has been used with people with mild to moderate intellectual disabilities. It will be administered at all treatment points.Readiness to Change Questionnaire (RCQ) [27], which has been shown to have good validity and reliability. It contains 12 statements that must be read to the person with mild to moderate intellectual disabilities. It will be administered at baseline and three months.Euro-QoL (EQ-5D-3 L); English version [28], which is a short questionnaire assessing general healthcare. This questionnaire has been used extensively in health research in the general population and more recently in studies of populations with intellectual disabilities. This will be administered at baseline and three months.Clinical Outcomes in Routine Evaluation (CORE-LD) [29], which is an adapted version of the instrument for people with intellectual disabilities and measures self-reported psychological distress. It will be administered at baseline and three months.Client Service Receipt Inventory (CSRI) [30], which is specifically adapted for the study to measure what services the client has been in receipt of in the past 6 months (for example, emergency room attendance, GP visits, benefits). It will be completed at baseline and three months for the previous three months. Data gathered by this tool will allow us to be more precise in recording the different services received by participants each study arm beyond the intervention and quantify the elements of ‘treatment as usual’.Sociodemographic details at baseline.

All instruments will be completed by research assistants in face-to-face assessments with participants and paid or family carers. These assessments will take place at a convenient location. AH and KS will train Research assistants in interviewing techniques for people with intellectual disabilities, how to assess capacity to consent to research and how to administer the study instruments.

#### Randomisation and masking

Randomisation will be conducted by contacting an external researcher once the potential participant has consented to take part in the study and baseline data have been collected (class A method of randomisation). The research team statistician will generate the randomisation list. Any breach in blinding/unmasking, a common problem with single blind trials, will be monitored to ensure that the research assistants are not aware, as far as possible, to which group the individual was allocated. The researchers will make a note of which group he/she believes the participant has been allocated to for all participants and this will be compared to the actual allocations at the end of the study. The database management will be supervised by the PRIMENT Clinical Trials Unit and the study statistician GB.

#### Treatment fidelity

We will develop a short scale to measure how the treatment is delivered and which components are used in each session, guided by the literature [31]. Ten per cent of the audiotaped sessions will be rated by KS, who has no contact with the therapist. The therapist will be supervised regularly throughout the study duration by CK.

#### Statistical analysis

The analysis of the data will be mainly in terms of descriptive statistics and point and interval estimations with the express aim to inform a future multicentre trial. No hypothesis testing will be performed. We will compare drop-out rates in the intervention and treatment-as-usual arm, and means, medians, interquartile ranges, counts and proportions to estimate effect size will be calculated. Regression models allowing for participant clustering will be considered to examine the association between the primary outcome and sociodemographic and clinical predictors. The results will be presented with 95% confidence intervals.

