### Aims and objectives

The key research question is: Can we design a large scale, randomised controlled trial (RCT) that will answer whether EBI is more effective than usual care in helping adults with mild to moderate intellectual disability to reduce their alcohol intake?

The feasibility trial will compare the use of EBI with treatment as usual in the participating areas and will enable us do the following:measure the number of eligible participants, including paid and family carers, willingness of clinicians to recruit participants, recruitment rate, loss to follow-up, adherence to the intervention, and standard deviation of the primary outcome measures. This will ultimately inform the sample-size calculation for a multicentre clinical trial.determine the acceptability of randomisation to service users through its effect on dropout rates and qualitative interviews.determine, through response rates to questionnaires, the appropriateness and the acceptability of the outcome measures to service users and their carers in order to explore the suitability of our chosen secondary outcome measures, that is, days abstinent, service use and health-related quality of life.estimate the time needed to collect and analyse dataexplore the utility of the health-related quality of life questionnaire in allowing the estimation of quality-adjusted life years in the sample.

We will also conduct qualitative interviews with service users, their carers, and service providers, to assess the acceptability of the treatment and to explore their experience of the treatment including any barriers and/or facilitators to taking part in the study. Findings from these interviews will enable us to refine the EBI.

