### Stage 2-Feasibility study

#### Design

This will be a single blind, randomised controlled trial of individual EBI delivered as an adjunct to usual care for alcohol use disorders (AUD). Fifty participants, randomised to either the intervention arm or usual care, will be assessed at baseline, two months and three months. Research assistants carrying out assessments will be blind to the trial arm to which the participants are allocated.

Finally, qualitative interviews will be carried out at three months (see stage 3 below).

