#### Participants

Fifty adults with mild to moderate intellectual disabilities aged 18 years and over, and who are known to professionals within the intellectual disabilities services as possibly having an alcohol problem, will be eligible to be referred to the study. Each participant should have a carer or family member prepared to accompany them to their sessions and complete the study instruments. Further justification for the sample size is available from http://www.nihr.ac.uk/CCF/RfPB/FAQs/Feasibility_and_pilot_studies.pdf.

Following informed consent, the participants will be assessed with the Wechsler Abbreviated Scale for Intelligence (WASI) [23] to ascertain their level of cognitive functioning (unless results from a previous cognitive assessment are available).

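### The arm effect on AUDIT is to come from raw summaries, with no baseline-adjusted estimate named and no statement of which SD will size the definitive trial

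*Protocol article*

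**What the plan says.** The Statistical analysis section of the protocol article describes estimation without hypothesis tests, aimed at informing a later multicentre trial, with results given as 95% confidence intervals. On the effect it says that "means, medians, interquartile ranges, counts and proportions to estimate effect size will be calculated". On modelling it says: "Regression models allowing for participant clustering will be considered to examine the association between the primary outcome and sociodemographic and clinical predictors".

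Aims and objectives lists the quantities to be learned, among them the "standard deviation of the primary outcome measures. This will ultimately inform the sample-size calculation for a multicentre clinical trial". It does not say whether this is the SD at baseline, at follow-up, of the change, or of the residual after adjustment.

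Under Outcome measures, "The primary outcome is a reduction in alcohol intake", measured by the modified AUDIT. Under Inclusion criteria, entry requires an AUDIT score above 8, with a cap on the sum of questions 4 to 6. The same section puts the share of adults with mild or moderate intellectual disability in contact with services who meet an AUDIT cut-off of 8 at 22.5%. Under Instruments, AUDIT is given at every time point. Under Design: "Fifty participants, randomised to either the intervention arm or usual care, will be assessed at baseline, two months and three months".

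**The concern.** The entry criterion and the primary outcome are the same scale, and everyone has a baseline value. In that setting the usual estimate of an arm effect is the difference in follow-up score adjusted for baseline. The article instead ties the effect to raw summaries and gives regression another purpose.

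Three things follow.

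- **Precision.** The raw difference discards information already collected and carries any chance imbalance in baseline AUDIT, which can be sizeable with about 25 per arm.
- **Within-arm reductions.** People selected for a high score tend to score lower on retest. A raw fall in AUDIT within an arm therefore includes regression to the mean.
- **Choice of SD.** Selection restricts the baseline spread, so the baseline SD is smaller than the follow-up SD in the same people. As the planning SD is not identified, someone using the results later could pick the wrong one.

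An adjusted analysis in the definitive trial would be sized from the residual SD, or equivalently from the follow-up SD and the correlation. The article commits to neither.

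**Working it through.** The plan has no figure to reproduce. The sample of 50 comes without alpha, power, target effect or SD; the Participants section points to an external link. What follows is an illustration.

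**Inputs**
- From the article: 50 participants in two arms; 22.5% above the cut-off.
- Assumed: 25 per arm (no allocation ratio is given), no dropout, a normal AUDIT score in the unselected population (SD = 1), and an unselected baseline-to-follow-up correlation r of 0.5 to 0.8.

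**Step 1: baseline after selection.** The upper 22.5% of a standard normal starts at z = 0.755.
- Mean λ = φ(0.755)/0.225 = 1.333.
- Variance v = 1 + zλ − λ² = 1 + 1.007 − 1.777 = 0.230, so the baseline SD is 0.480.

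**Step 2: follow-up, change and residual in the selected group.**
- Follow-up variance = 1 − r² + r²v
- Change variance = (1 − r)²v + 1 − r²
- Residual variance given baseline = 1 − r²
- In-sample correlation = r√v / follow-up SD
- Mean fall with no treatment effect = (1 − r)λ

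| r | Follow-up SD | Change SD | Residual SD | In-sample correlation | Untreated fall |
|---|---|---|---|---|---|
| 0.5 | 0.899 | 0.899 | 0.866 | 0.267 | 0.67 |
| 0.6 | 0.850 | 0.823 | 0.800 | 0.339 | 0.53 |
| 0.7 | 0.789 | 0.729 | 0.714 | 0.426 | 0.40 |
| 0.8 | 0.712 | 0.608 | 0.600 | 0.539 | 0.27 |

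All entries except the correlation are in unselected SD units.

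**Step 3: precision of the arm difference, in follow-up SD units.**
- Unadjusted: t(48 df) × √(2/25) = 2.011 × 0.283 = 0.57.
- Adjusted, r = 0.6: 2.012 × 0.283 × √(1 − 0.339²) = 0.569 × 0.941 = 0.54.
- Adjusted, r = 0.8: 0.569 × √(1 − 0.539²) = 0.569 × 0.842 = 0.48.

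**Step 4: what this means for n** (variance ratios).
- Adjusted against raw follow-up: 0.929 (r = 0.5) to 0.710 (r = 0.8), so n is 7% to 29% lower.
- Adjusted against raw change: 0.929 (r = 0.5) to 0.975 (r = 0.8), so n is 7% to 3% lower.

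**Step 5: which SD is carried forward.** Take r = 0.7, an assumed effect of 0.3 unselected SD, 80% power and two-sided 5%, with n per arm = 2(1.960 + 0.842)²σ²/0.3². This gives 109 on the follow-up SD, 93 on the change SD, 89 on the residual SD and 41 on the baseline SD.

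**Step 6: bias.** In 5,000 simulated trials of 25 per arm with a true effect of −0.30, the mean estimates from raw follow-up, raw change and baseline adjustment were all −0.30 or −0.31, at r = 0.5 and at r = 0.7. Empirical standard errors, in that order, were 0.250, 0.253 and 0.245 at r = 0.5, and 0.224, 0.207 and 0.205 at r = 0.7.

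**Step 7: uncertainty of any SD from this trial.** With 48 df the 95% limits are 0.83 and 1.25 times the estimate. The implied n runs from about 0.70 to 1.56 times.

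**The case against.** The strongest reply is that this is a condensed article and a full analysis plan may name the model. Point and interval estimation does not exclude an adjusted estimate, the clinical predictors could include baseline AUDIT, and allowing for participant clustering hints at a repeated-measures model. That is fair as far as it goes. But the article does not simply stay silent: it states how the effect size is obtained and gives regression a different purpose, in which arm is not named. That published statement needs amending even if a fuller plan goes further.

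Three stronger readings are tempting, and the document does not support them.

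- **That the effect estimate is biased by selection on AUDIT.** Regression to the mean has the same expectation in both randomised arms and cancels in the comparison, as Step 6 shows. Nothing in the article says that within-arm falls will be presented as treatment effects.
- **That the definitive trial will be undersized two- to three-fold.** That would require sizing on the baseline SD (ratios of 2.2 at r = 0.8 to 3.1 at r = 0.6). No section says so, and since the primary outcome is a reduction, a follow-up or change SD is the more natural reading.
- **That adjustment would bring the half-width down to about 0.41.** That needs an in-sample correlation of 0.7. Selection weakens the correlation, so under this model the unselected value would have to be about 0.90.

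The model itself is also open to challenge. AUDIT is bounded and capped through questions 4 to 6. The 22.5% refers to a cut-off of 8 among service users generally, whereas participants are those already suspected of an alcohol problem, so truncation may be milder. This makes the figures illustrative; it does not remove the case for adjustment.

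**Conclusion.** The point holds as a modest improvement, not as an error that invalidates the trial. The stated route to the effect size leaves out baseline adjustment although the covariate is measured in everyone and defines entry. The SD promised for planning is not identified.

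At 25 per arm, adjustment takes the 95% CI half-width from 0.57 to about 0.54 to 0.48 follow-up SD for assumed unselected correlations of 0.6 to 0.8. Against raw change the gain is only about 3% to 7% in n over correlations of 0.5 to 0.8. The raw arm difference remains unbiased. The ambiguity over the SD matters because the candidates differ, most of all the baseline SD, but there is no evidence that the wrong one would be chosen. These sizes rest on the truncated-normal model, equal arms, no dropout and assumed correlations.

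**What to change.** In the Statistical analysis section, state that the arm effect is estimated by regressing follow-up AUDIT on arm and baseline AUDIT, and that the adjusted difference at three months is reported with its 95% CI. A repeated-measures version may use both the two- and three-month scores. The raw summaries can stay as description.

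In the same place, and in Aims and objectives, state that the planning quantities are the follow-up SD, the residual SD with its confidence interval, and the baseline-to-follow-up correlation. Add that neither the baseline SD nor within-arm change will be used to size the definitive trial.

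The cost is a few sentences and a little programming, with no extra data or visits. How cautiously the later trial uses the estimated SD, and which target difference it adopts, are decisions for that trial and need not be settled here.

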#### Economic evaluation and analysis

The feasibility of collecting information for a full randomised control trial (RCT) cost-effectiveness analysis will be assessed, based on cost per gain in outcome of EBI compared to treatment as usual from a health and social care cost perspective. Costs will include the intervention, training and health and social care provision. Health and social care resource use, employment and the impact on carers will be costed using national published values. The feasibility of a cost-effectiveness analysis from a societal cost perspective will also be assessed. Descriptive statistics for these variables will be reported and an initial analysis will calculate 1) the mean incremental cost per reduction in days of heavy drinking and 2) the mean cost per quality adjusted life year (QALY) gained using the EQ-5D mapping algorithm. Previous studies in the general population have found that generic quality of life measures are not sensitive to reductions in alcohol misuse, particularly in hazardous drinkers [32]. We will test whether this is also the pattern in adults with mild to moderate intellectual disabilities and whether we can use these measures in a full trial using correlations, regression analysis and mapping. Some of the impact from long-term hazardous and harmful alcohol misuse can occur well into the future. Due to the short follow-up period, it is unlikely that the long-term impact will be captured within this trial, but this will require further investigation as part of a full trial using decision analytical models.

### Stage 3-Qualitative study

In order to assess the perceived acceptability and usefulness of the intervention, 50% of service user and carer dyads allocated to the EBI arm of the trial, will be interviewed at end of treatment (that is, 12 weeks). The interviews will be completed by the two service users who are supported to contribute to the study reference group (part of the trial management group), with support from the research assistants. Both service users and the research assistants will be trained in how to collect qualitative data and conduct the interviews. We will include participants who may have dropped out of treatment, if at all possible, in order to ascertain their perceptions of the intervention and their reasons for dropping out. Interviews will be audiotaped and analysed using content analysis and/ or thematic analysis [33,34].

### Ethical and research and development reviews

The study has been approved by the NRES Committee South Central - Berkshire (REC reference 13/SC/0143).

All study personnel will comply with the MCA 2005 [35] and published research governance guidelines. We anticipate that all participants will have capacity to consent and sufficient verbal communication skills to take part in the treatment and in the qualitative interview. All patient information sheets and consent forms will be in easy-read versions, and informed written consent will be obtained from all participants. As this is a non-invasive intervention, we do not anticipate any adverse events, but we will follow safety reporting guidance issued by the National Research Ethics Service (UK) for studies except clinical trials of investigational medicinal products.

The study has been approved by the Research and Development departments of the following organisations: Hertfordshire Partnership NHS Foundation University Trust, Camden and Islington NHS Foundation Trust, Surrey and Borders Partnership NHS Foundation Trust.

### Patients and public involvement

We consulted with a service user group based in one of the research areas on two different designs for the study, one being the current version and the other a feasibility study of contingency management. The latter is defined as treatment based on principles of behaviour modification and aims to incentivise and then reinforce changes in behaviour with the aid of vouchers, privileges, prizes or modest financial incentives that are of value to the client (https://www.nice.org.uk/guidance/cg51/chapter/appendix-c-contingency-management-key-elements-in-the-delivery-of-a-programme). Based on the various issues identified as potential difficulties in each option, we made the decision to start from a simpler project that has yet to be tested in this population. An easy-read version of the project proposal was presented to a service users’ group for advice and comments on how to present the study and describe the intervention. Two service users and their carers contribute to the trial steering committee and will conduct the qualitative interviews as described earlier. The service users will be involved in the interpretation of the interviews, write up the findings in an accessible format and disseminate them locally and nationally.

## Discussion

The study will provide invaluable information on several aspects of alcohol and other substance misuse patterns in people with intellectual disability. Although not an epidemiological study per se, it will reveal important elements of treatment pathways and support needs for those individuals. Such information is currently either not available or mostly derived from clinic populations. Our sample will be drawn from a wide variety of community care.

Furthermore, there is limited literature on use of alcohol instruments such as AUDIT and RCQ in people with intellectual disabilities; therefore, the adapted tools used in this project will be particularly useful for further research but also in clinical practice in this field.

Most importantly, there is emerging debate about the impact of brief interventions delivered in primary care on alcohol problems [36]. Current literature suggests that they indeed reduce consumption, but there is little information on the content and fidelity of the intervention in published studies.

In carrying out the study, we will need to overcome generic difficulties in research in adults with substance misuse who may be not only be hard to reach but also unwilling to commit to treatment or may drop out. Access to participants may depend on local configurations of services, and therefore, the recruitment strategy will be crucial in carrying out the feasibility study. Therefore, our work will be sufficiently novel to contribute not only to the field of intellectual disabilities but to the existing research in this particular topic.

## Trial status

At the time of the manuscript submission the trial is still recruiting new participants.

## Abbreviations

AUDIT: Alcohol Use Disorders Identification Test
EBI-ID: extended brief intervention-ID
ID: intellectual disabilities
RCT: randomised controlled trial
IQ: intelligence quotient
